### 3.2. DNA Extraction

DNA will be extracted from the stool samples (0.3 g) using a Qiagen DNeasy PowerSoil Pro kit (Qiagen, Hilden, Germany, cat# 47014). However, instead of vortexing, the samples will be subjected to physical lysis in a bead-beater (FastPrep 24, MP Biomedicals, Irvine, CA, USA) for 1 min at 6.5 m.s. DNA will be eluted in molecular-grade water and stored at −80 °C.

### 3.3. Quantification of SCFA

A modified gas chromatography–mass spectrometry (GC-MS)-based method will be used to extract and analyse SCFAs from the faecal samples. Acetic acid, propionic acid, isobutyric acid, butyric acid, isovaleric acid, 4-methyl valeric acid (internal standard, IS), ethyl acetate, and meta-phosphoric acid will be purchased from Merck (Singapore). For sample preparation, 0.2 g of the faecal sample will be first diluted 5-fold in 1 mL of 1% phosphoric acid and frozen at −20 °C immediately after collection. Before SCFA extraction, the frozen samples will be thawed and added to 100 μL of 10% meta-phosphoric acid solution to adjust the pH to around 2. The samples will be homogenized by vortexing for about 10 min and centrifuged for 30 min at 20,817× *g*. After that, 1 mL of aqueous supernatant will be transferred into a new tube, and 4-methyl valeric acid will be added to achieve a final concentration of 500 μM. Then, the mixture will be vortexed for 30 min and centrifuged for 10 min at 20,817× *g* after addition of 500 μL of ethyl acetate. Then, 2 μL of the organic extracts will be injected in splitless mode into an Agilent GC-MS system (Agilent Technologies (Santa Clara, CA, USA) 7890B-5977B Bundle with Stainless Steel Source) and separated using an HP-FFAP capillary column (30 m × 0.250 mm × 0.25 μm; Agilent, Santa Clara, CA, USA). Helium will be used as the carrier gas at 1 mL/min. The column temperature will initially be 80 °C (1 min), and then increased to 120 °C at 20 °C/min, and finally to 210 °C at 6.13 °C/min and kept at this temperature for 2 min. The solvent delay will be 3.5 min. The detector will be operated in SIM acquisition mode with 30–250 *m/z* range. The injector, ion source, quadrupole, and interface will be set at 250 °C, 230 °C, 150 °C, and 280 °C, respectively. SCFAs will be identified by comparing with the standards and double-confirmed with the NIST 17 library. Quantification will be performed using Mass Hunter Quantitative software (version B.09.00), with base peak ion selected as the quantifier for each SCFA. Calibration graphs will be constructed by plotting relative response (ratio of peak area of SCFA/peak area of IS) versus relative concentration for each SCFA. Final concentrations will be expressed as microgram of SCFA per gram wet weight faecal sample. All analyses will be performed in duplicate. Wilcoxon rank analysis will be performed to compare the SCFA concentrations between the different groups.

### 3.4. Linearity and Sensitivity of SCFA

A stock solution containing a mixture of standards (20 mM final concentration each) in ethyl acetate will be diluted to obtain a calibration curve ranging from 2 to 15,000 μM. This will be added to each diluted standards mixture (500 μM final concentration). Calibration graphs will be constructed by plotting the ratio of peak area SCFA/peak area IS vs. concentration for each individual SCFA. By normalizing the peak area to that of the IS, the variability in the extraction step and the instrument response will be corrected (in particular, the injection volume variability and the MS response). Each point of the calibration graph shall correspond to the mean value from independent replicate injections. The limits of detection (LOD) and quantification (LOQ) of the individual analytes will be obtained by injecting successively more diluted standard solutions and will be calculated according to the International Union of Pure and Applied Chemistry 16 method [34] based on a signal-to-noise ratio (S/N) of 3 for the LOD and of 10 for the LOQ.

### 3.5. Quantification of Faecal Bile Acids

#### 3.5.1. Faecal Bulk Bile Acid Concentration

A total of 100 mg of lyophilized stool will be heated to 195°C in 1 mL of ethylene glycol KOH for 2 h, neutralized with 1 mL of saline and 0.2 mL of concentrated HCl, and then will be extracted into 6 mL of diethyl ether thrice. After the evaporation of ether, the sample residues will be dissolved in 6 mL of methanol and subjected to enzymatic analysis. The enzymatic reaction mixtures will incorporate 66.5 mmol/L Tris, 0.33 mmol/L EDTA, 0.33 mol/L hydrazine hydrate, 0.77 mmol/L NAD (N 7004, Sigma-Aldrich, St. Louis, MO, USA), 0.033 U/mL 3-hydroxysteroid dehydrogenase (Sigma-Aldrich, St. Louis, MO, USA), and either the sample or the standard (taurocholic acid; Sigma-Aldrich, St. Louis, MO, USA) dissolved in methanol. After 90 min of incubation at 37 °C, absorbance will be measured at 340 nm.

#### 3.5.2. Measurement of Primary and Secondary Bile Acids

200 mg of glass beads will be added to a suspension of ~100 mg of stool and 0.25 mL of water in a 1-dram Teflon-capped glass vial. Vortexing for 60–90 s will be performed to homogenise the suspension. Ethanol (1.8 mL) will be added, and the suspension will be heated by stirring in a heating block at 80 °C for 1.5 h. The sample will be cooled, transferred to a 2 mL Eppendorf tube, and then centrifuged at 13,500 rpm for 1–2 min. The supernatant will be removed and retained. The pellet will be resuspended in 1.8 mL of 80% aqueous ethanol, transferred to the original vial, and then heated to 80 °C for 1.5 h. The sample will be centrifuged again, and the supernatant removed and added to the first extraction supernatant. The pellet will now be resuspended in 1.8 mL of chloroform–methanol (1:1 *v*/*v*) and refluxed for 30–60 min. The sample will be centrifuged, and the supernatant will be removed and concentrated to dry on a rotary evaporator. The ethanolic supernatants will be added to the same flask, the pH will be adjusted to neutrality by adding aqueous 0.01 N HCl, and the combined extracts will be dried. The dried extract will be resuspended in 1 mL of 0.01 N aqueous HCl by sonication for 30 min. A BIO-RAD Poly-Prep chromatography column (0.8 × 4 cm) will be loaded with Lipidex 1000 as a slurry in MeOH, allowed to pack under gravity to a final volume of 1.1 mL, and will be washed with 10 mL of distilled water. The suspension will be filtered through a bed of Lipidex 1000, and the effluent will be discarded. The flask will be washed with 3 × 1 mL of 0.01 N HCl, the suspension will be passed through gel, and the bed washed with 4 mL of distilled water. Bile acids and sterols will be recovered by elution using a Lipidex gel bed with 8 mL of methanol. A BIO-RAD (Hercules, CA, USA) Poly-Prep chromatography column (0.8 × 4 cm) will be loaded with washed SP-Sephadex as a slurry in 72% aqueous MeOH to a final volume of 1.1 mL. Methanolic extract will be passed through the SP-Sephadex column, and the column will be washed with 4 mL of 72% aqueous methanol. The extract and suspension will be combined, and the pH will be brought to neutral with 0.04 N aqueous NaOH. A BIO-RAD Poly-Prep chromatography column (0.8 × 4 cm) will be loaded with Lipidex-DEAP, prepared in acetate form, as a slurry in 72% aqueous MeOH to a final volume of 1.1 mL. The combined neutralized effluent will be applied to the column, and the solution will be eluted using air gas pressure (flow rate ~25 mL/h). The flask and column were washed with 2 × 2 mL of 72% aqueous ethanol, and the sample and liquid will be combined to give a fraction of neutral compounds, including sterols. Unconjugated bile acids will be eluted using 4 mL of 0.1 M acetic acid in 72% (*v*/*v*) aqueous ethanol adjusted to pH 4.0 by the addition of concentrated ammonium hydroxide. The fraction containing bile acids will be concentrated to dry on a rotary evaporator.

The bile acids will be converted to their corresponding methyl ester derivatives by adding 0.6 mL of MeOH followed by 40 µL of 2.0 M solution of (trimethylsilyl)diazomethane in diethyl ether. The solution will be divided in half, and each half of the sample will be concentrated to dry on a rotary evaporator. Bile acids in the first half of the sample will be converted to their corresponding trimethylsilyl ether derivatives by the addition of 35 µL of 2:1 solution of N,Obis(trimethylsilyl)trifluoroacetamide and chlorotrimethylsilane, and then will be analysed by GC-MS. The identities of individual bile acids will be determined by the comparison of retention time and fragmentation pattern to known standards. Both the ratio of cholest-3-ene to deoxycholic acid in the sample and the amount of internal standard to be added shall be determined by integrating the peak areas. A known amount of internal standard, 5^®^-cholestane-3^®^-ol (5^®^-coprostanol), shall be added to the second half of the sample (0.003–0.07 mmol). Bile acids in the second half of the sample will be converted to their corresponding trimethylsilyl ether derivatives by the addition of 35 µL of 2:1 solution of N,O-bis(trimethylsilyl)trifluoroacetamide and chlorotrimethylsilane, and then will be analysed by GCMS [35,36,37]. 

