### 2.11. Secondary Outcomes

Faecal short-chain fatty acids (SCFAs) and bile acids will be quantified in the first week of life (T1), and again four months after probiotic supplementation (T2). Growth parameters, including weight, length, and head circumference, will be assessed at 4 (T2), 12 (T3), and 24 (T4) months of age. Developmental parameters will be evaluated using the Ages and Stages Questionnaire (ASQ) and the ASQ-Social Emotional scale, 2nd version, at 4, 12, and 24 months of age.

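### The bile-acid internal standard is added too late to correct for losses in extraction, columns and methylation, which costs precision in the absolute amounts of individual bile acids

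*Protocol article*

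**What the plan says.** Section 2.11 makes bile acids a secondary outcome at two time points: "Faecal short-chain fatty acids (SCFAs) and bile acids will be quantified in the first week of life (T1", and again at four months. Section 3.5 describes two assays. Section 3.5.1 is an enzymatic assay of the bulk concentration. Section 3.5.2 measures individual primary and secondary bile acids by GC-MS.

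The 3.5.2 assay begins without any standard: "200 mg of glass beads will be added to a suspension of ~100 mg of stool and 0.25 mL of water". Two ethanolic extractions and a chloroform–methanol reflux follow, with drying steps. Then come three columns:

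- Lipidex 1000: "The suspension will be filtered through a bed of Lipidex 1000, and the effluent will be discarded", after which the retained material is recovered in methanol.
- SP-Sephadex: "Methanolic extract will be passed through the SP-Sephadex column".
- A third column that "will be loaded with Lipidex-DEAP, prepared in acetate form". Here the first liquid through is collected "to give a fraction of neutral compounds, including sterols", and the unconjugated bile acids are eluted afterwards.

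Next, "The fraction containing bile acids will be concentrated to dry on a rotary evaporator". The acids are methylated, the solution is split into two portions, and both are dried. The first portion is silylated and run to identify the acids and to decide how much standard to use. Only then does coprostanol enter the assay: it "shall be added to the second half of the sample", just before silylation and GC-MS.

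**The concern.** A standard corrects only for what happens after it is added. Here that is silylation and injection. Bile acid lost during extraction, on the columns, in drying or through incomplete methylation is read as bile acid that was never in the stool. An uneven division of the sample acts the same way.

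The article itself treats correction for extraction as worth having. For short-chain fatty acids, Section 3.3 adds the internal standard before the ethyl acetate extraction, and Section 3.4 says that normalising to it corrects for variability in that step. The bile-acid procedure is much longer, yet its standard covers only the end of it.

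At stake is the precision of a secondary outcome compared between arms of 30 infants, and the meaning of the absolute levels reported.

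**Working it through.** **1. Order of steps in 3.5.2**

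| Step | Standard present? |
|---|---|
| Stool weighed and homogenised | No |
| Two ethanolic extractions, chloroform–methanol reflux, drying | No |
| Lipidex 1000, SP-Sephadex and Lipidex-DEAP columns | No |
| Drying, methylation | No |
| Division into halves, drying of each | No |
| Coprostanol added to the second half | Added here |
| Silylation, GC-MS | Yes |

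**2. Effect on the reported value**

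Let R be the fraction of a bile acid that survives to the point of addition. Then

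reported amount = R × true amount.

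For illustration, R = 0.70 is read as 1 − 0.70 = 30% less bile acid. On the log scale,

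log(reported) = log(true) + log(R).

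A constant R shifts every sample by the same amount. It leaves ranks and differences between arms on the log scale unchanged, and lowers only the absolute level. If R varies between samples independently of arm, it adds variance:

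total SD = √(SD_infant² + SD_recovery²).

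If R is the same for all acids within a sample, it cancels in the proportion of one acid to the total. Losses specific to one acid do not cancel.

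**3. Scale, on assumed values**

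The article gives no recovery figure, no bile-acid SD and no power statement for bile acids. There is therefore no figure of the plan to reproduce. The inputs are:

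- 30 per arm (Section 2.9, where it is justified for alpha diversity);
- two-sided test at 0.05 (Section 3.7);
- assumed: SD_infant 0.6 to 0.8 on the log scale;
- assumed: SD_recovery 0.15, 0.30 or 0.40 on the log scale;
- assumed: a true effect that would give 80% power if recovery were perfect.

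For a two-sample t-test with 30 per arm, 80% power needs a standardised difference of d = 0.736. With recovery noise this becomes

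d′ = 0.736 / √(1 + SD_recovery² / SD_infant²).

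| SD_recovery | SD_infant | Variance ratio | d′ | Power |
|---|---|---|---|---|
| 0.15 | 0.6 | 1 + 0.0225/0.36 = 1.06 | 0.714 | 78% |
| 0.15 | 0.8 | 1 + 0.0225/0.64 = 1.04 | 0.723 | 79% |
| 0.30 | 0.6 | 1 + 0.09/0.36 = 1.25 | 0.658 | 71% |
| 0.30 | 0.8 | 1 + 0.09/0.64 = 1.14 | 0.689 | 75% |
| 0.40 | 0.6 | 1 + 0.16/0.36 = 1.44 | 0.612 | 64% |
| 0.40 | 0.8 | 1 + 0.16/0.64 = 1.25 | 0.658 | 71% |

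At a recovery SD of 0.30, recovering the lost precision through numbers would take about 30 × 1.14 = 34 to 30 × 1.25 = 37.5 infants per arm. Section 3.7 plans Mann–Whitney tests for continuous data. The t-test stands in for them here to show scale only.

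**4. Would moving coprostanol to the start solve it?**

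No. Section 3.5.2 sends sterols into the neutral fraction on the third column, before the bile acids are eluted. Coprostanol is a neutral sterol, so it would leave with that fraction. A recovery standard has to be an acid that travels with the bile acids.

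**The case against.** The strongest reply is that this is a condensed article. Section 3.5.2 cites published methods, and Section 3 says the methodology is identical to that of two earlier trials. A recovery check could sit in those sources, which are not shown. This stands as far as it goes: the absence of a recovery figure is not itself a fault. However, the compound, its amount and the point of addition are all stated, and as stated the standard cannot correct earlier losses.

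Other limits also stand:

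- The bulk assay in 3.5.1 does not use coprostanol and is untouched, though nothing says its total is used to rescale the individual acids.
- The article does not say whether 3.5.2 results will be amounts or proportions. Only amounts are exposed to losses shared by all acids.
- At a low recovery SD the loss of power is one or two percentage points.

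A reader might infer more than the text supports. One such inference is that laboratory losses could pass for a treatment effect. Allocation is randomised and outcome assessors are masked (Section 2.16), samples go to the laboratory only after recruitment ends (Section 3.1), and no run layout is given. Nothing points to losses that differ by arm. A second is that the approximate stool mass goes uncorrected; the text gives a nominal mass and does not say that the actual weight is unrecorded. A third is that the division into halves is crude; the text does not say how it is done.

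**Conclusion.** The point holds as a minor one about precision. In 3.5.2 the only internal standard corrects silylation and injection and nothing earlier. Variable recovery or an uneven split adds noise unrelated to arm to absolute amounts of individual bile acids, and absolute levels are understated. The comparison between arms is not biased, and the primary outcome and sample size are not affected.

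The size cannot be derived from the article. The power range of 64% to 79%, against 80% with perfect recovery, rests wholly on the assumed SDs and on a hypothetical effect. It runs from negligible to material, depending on a recovery SD that is not reported.

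**What to change.** In 3.5.2, add a known amount of an acidic bile-acid recovery standard that does not occur in stool, for example a deuterated or nor-bile acid, to the sample before the first ethanol extraction. It should be unconjugated, so that it elutes with the fraction that is analysed. Quantify the individual acids against it. Keep coprostanol as the injection standard, so that values comparable with the earlier trials can also be reported.

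The cost is one reagent, one more monitored peak per sample and a short validation of the standard through the three columns. No extra stool or infants are needed. Because samples go to the laboratory after recruitment is complete (Section 3.1), the change can be made before any sample is run.

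If the cited methods already include a recovery correction, one sentence in 3.5.2 stating it, with the recovery and its CV, settles the point.

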### 3.6. Microbiota Analysis

#### 3.6.1. PCR Amplification and 16S rRNA Gene Sequencing

Genomic DNA will be submitted to the laboratory for library preparation and sequencing on the Illumina (San Diego, CA, USA) MiSeq platform using the MiSeq Kit v3 (2 × 300 cycles) using V3–V4 primers.

#### 3.6.2. 16S rRNA Gene Sequence Analysis

16S rRNA sequence data will be quality filtered and trimmed using TRIMMOMATIC (version 0.36) truncating reads if the quality is below 12 in a sliding window of 4 bp. USEARCH (version 10.0.240) will be used to merge and filter high-quality sequencing reads between 350 and 500 nucleotides. Unique sequences that may appear less than 8 times will be removed. Processed reads will then be concatenated and clustered into operational taxonomic units (OTU) at 97% sequence similarity using UPARSE (USEARCH version 12). Chimeras will be removed de novo in reference mode using UCHIME (version 4.2.40) together with the SILVA SSURef NR99 database (version 132), and OTU sequences will be identified taxonomically using BLASTN (BLAST + version 2.14.0) alignments against the SILVA database (version 132).

For alpha diversity measures, each sample will be subsampled 100 times to a count of 20,000 counts per sample, and the average will be taken. OTU richness and diversity indices, Simpson, Shannon, ACE, and Chao1, will be calculated in R (version 3.6.0) using the vegan package (version 2.6-8). Relative abundance analysis at the Phylum, Family, Genus, and species levels will be carried out using phyloseq package (version 1.50.0) in R 4.4. The data will be visualized using the ggplot2 (version 3.5.1) and ggpubr (version 0.6.0) packages.

For beta diversity, both the weighted UniFrac and Bray–Curtis calculations will be used. For weighted Unifrac, the data will be transformed to relative abundance. To generate a phylogenetic tree for diversity computations, zOTUs will be aligned with MAFFT (version 7.526), and the tree will be calculated with FastTree (version 2.1.11). Weighted unifrac distances will be calculated and visualized on a principal coordinate analysis (PCoA) plot. For Bray–Curtis, the data will be square root transformed, and then visualized on a non-metric multi-dimensional (NMD) scaling plot.

#### 3.6.3. Shotgun Metagenomic Analysis

The quality of the sequencing reads will be checked using FastQC (version 0.11.9). Cutadapt (version 1.8.1) will be used for the quality-filtering of raw reads to remove adapters and low-quality bases using -e 0.1, -q 20, -and a minimum-length of 30 as parameters. Bowtie2 (version 2.3.5) will be used for mapping the trimmed reads with the reference database, and GRCH38 (version GRCh38.p14) will be used to remove human host reads using “–un-conc” and “–very-sensitive-local” as parameters.

#### 3.6.4. Taxonomic Profiling

Kaiju classifier (version 1.7.0) will be used for the taxonomic classification of metagenomic reads. The database index will be created from the reference database, nr_euk, downloaded from the source. MEGAN6 will be used for calculating the normalized read counts of bacteria at the species level. To obtain sub-species information for *Bifidobacterium longum*, Kraken2 (version 2.1.3) with the default database with ‘report option’ will be used. The read counts for each taxon are the number of reads covered by the clade rooted to this taxon.

### 3.7. Statistical Analysis of Clinical, SCFA, Bile Acid and Microbiome Data

Analysis will be based on the intention-to-treat principle. The continuous data will be summarized using median, interquartile range, and range. The categorical data will be summarized using frequency distributions. Univariate comparisons for the continuous data will be made using the Mann–Whitney test. For the categorical data, the Chi-square or Fisher exact test will be used.

The SCFA data will be analysed using a linear mixed model effect (LME) test to assess the differences between the groups over time. In this analysis, the subjects will be modelled as a random factor, and time and treatment are fixed factors. All the tests will be two-sided, and a *p*-value < 0.05 will be considered significant. The data on clinical outcomes will be analysed using SPSS version 22.0 statistical software (Armonk, NY, USA: IBM Corp.) and SCFA in R (version 3.5.1).

**Pre-planned subgroups:** (1) Infants who are born through caesarean section due to increased risk of gut dysbiosis. (2) Infants born to mothers with diet-controlled vs. insulin-dependent GDM. (3) Infants born to mothers with GDM and a normal vs. high BMI.

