### 2.9. Sample Size Calculation

A sample size of 30 per group (total 60) was considered adequate to detect a 1.5-fold difference in alpha diversity with 80% power and a significance level of 0.05. By focusing on biological relevance, this sample size ensures that even subtle changes in microbial composition can be detected, providing a robust foundation for understanding the underlying biological mechanisms. This sample size allows for the detection of biologically meaningful variations in microbial composition, ensuring that differences in diversity metrics, such as Shannon diversity or Bray–Curtis dissimilarity, are statistically significant. By focusing on these well-defined biological parameters, this study can reliably capture important variations in microbial communities, providing a strong foundation for understanding their role in the system under investigation [21,22,23].

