### 2.10. Primary Outcome

Faecal microbiome composition will be estimated using 16S rRNA and shotgun sequencing. Baseline gut dysbiosis will be assessed at Timepoint 1 (T1: first week of life) by evaluating the ratio of beneficial to pathogenic bacteria, with reductions in dysbiosis measured at Timepoint 2 (T2: after four months of supplementation) in the probiotics group compared to the placebo group. The following variables will be analysed: (1) the presence or absence of specific species or pathways and clusters based on the unsupervised clustering of the gut microbial profile; (2) alpha diversity, richness, the abundance of particular species or pathways, and the differences in these numeric variables (treatment vs. baseline).

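### For the microbiome outcomes, change from T1 is listed beside T2 levels with no main contrast named, and the only stated test ignores T1 and delivery mode; change scores could cost 18 to 22 points of power

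*Protocol article*

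**What the plan says.** Section 3.7 of the protocol article covers clinical, SCFA, bile acid and microbiome data. For continuous variables it says: "Univariate comparisons for the continuous data will be made using the Mann–Whitney test". A model is specified only for SCFA: a linear mixed model with subject as random factor and time and treatment as fixed factors. On error rate, "All the tests will be two-sided, and a *p*-value < 0.05 will be considered significant".

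Section 2.10 makes microbiome composition the primary outcome. Its numeric variables are alpha diversity, richness and abundances, together with "the differences in these numeric variables (treatment vs. baseline"). Levels and changes therefore stand side by side, and neither is named as the main contrast.

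Delivery mode enters the analysis only as the first pre-planned subgroup: "Infants who are born through caesarean section due to increased risk of gut dysbiosis". The Discussion also lists it among the factors that shape the infant microbiota. Section 2.16 describes randomisation in blocks of 2 and 4 and mentions no strata.

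Section 2.9 sizes the trial at 30 per group for a "1.5-fold difference in alpha diversity with 80% power and a significance level of 0.05".

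**The concern.** A change score carries the noise of both samples. If T1 and T2 have the same SD and correlate below 0.5, the change is more variable than the T2 value alone. Stool from the first week of life and stool at four months may well correlate weakly, and the plan would then use its baseline in a way that lowers power.

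ANCOVA on T2 with T1 as covariate avoids this, because it uses the baseline only as far as it predicts T2. Delivery mode has to be recorded for the planned subgroup, so it is available as a covariate too.

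Two things are at stake in a trial of 60 infants: power for the primary outcome, and the freedom to choose between level and change after seeing results. A Mann–Whitney p-value also gives no treatment difference with a confidence interval.

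**Working it through.** **The plan's own figure.** On the log scale the target is ln(1.5) = 0.405. Section 2.9 gives no SD, so 30 per group cannot be verified. With two-sided alpha 0.05 and 80% power, n per arm is 16, 24, 30, 35, 47 and 62 at log-scale SDs of 0.4, 0.5, 0.56, 0.6, 0.7 and 0.8. Only an SD near 0.56 returns 30. The implied standardised difference is d = √2 × (1.960 + 0.842)/√30 = 0.723, and 0.405/0.723 = 0.56. This d is a back-calculated assumption. It sets an unadjusted comparison of T2 means at 80% power.

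**Inputs.** The article gives 30 per arm, two-sided alpha 0.05, and the tests and variables described above. The T1–T2 correlation ρ is assumed and varied from 0 to 0.7. Normal data and equal SDs at T1 and T2 are also assumed.

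**Formulas.** Power = Φ(d × √(n/(2V)) − 1.96) = Φ(2.802/√V − 1.96), where V is the variance relative to T2 alone:
- T2 alone: V = 1
- change score: V = 2(1 − ρ)
- ANCOVA on T1: V = 1 − ρ²
- Mann–Whitney: as for the mean comparison, with n multiplied by 0.955.

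**Example, ρ = 0.2.** Change: V = 1.6, so Φ(2.215 − 1.96) = 60.1%. ANCOVA: V = 0.96, so Φ(2.859 − 1.96) = 81.6%. The gap is 21.5 points.

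| ρ | Change score | ANCOVA | Gap | Mann–Whitney on change | Mann–Whitney on T2 | ANCOVA minus Mann–Whitney on T2 |
|---|---|---|---|---|---|---|
| 0 | 50.8% | 80.0% | 29 | 49.0% | 78.2% | 2 |
| 0.2 | 60.1% | 81.6% | 22 | 58.1% | 78.2% | 3 |
| 0.3 | 65.8% | 83.6% | 18 | 63.8% | 78.2% | 5 |
| 0.5 | 80.0% | 89.9% | 10 | 78.2% | 78.2% | 12 |
| 0.7 | 95.1% | 97.5% | 2 | 94.2% | 78.2% | 19 |

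The rank test itself costs about 2 points under normality (80.0% against 78.2%). Applied to change scores, its gap to ANCOVA is 24 points at ρ = 0.2 and 20 at ρ = 0.3.

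**Check by simulation** (4,000 trials per ρ). At ρ = 0.2, Mann–Whitney on change has 55.8% power, Mann–Whitney on T2 75.5% and ANCOVA 79.0%. At ρ = 0.3 the figures are 62.1%, 75.6% and 81.7%. The pattern is the same.

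**Unequal SDs.** If the T1 SD is k times the T2 SD, the change-score factor becomes 1 + k² − 2kρ, while the ANCOVA factor is unchanged. At these low correlations the loss shrinks if first-week values vary less than four-month values, and grows if they vary more.

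**Delivery mode.** If it explained a further 10% of variance (assumed), ANCOVA power would be 84.0%, 85.6%, 87.6% and 93.5% at ρ = 0, 0.2, 0.3 and 0.5, about 4 points more. At 5% the gain is about 2 points. The chance that the arms differ by 20 percentage points or more in caesarean births (6 or more of 30) is 12.0%, 14.7% or 15.5% if 30%, 40% or 50% of births are caesarean (assumed).

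**The case against.** A reader might infer that unadjusted Mann–Whitney testing of continuous outcomes in general costs about 20 points of power. The documents do not support that, for these reasons.

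- **Source of the loss.** It belongs to change scores at low correlation. A rank test on T2 loses only 2 to 5 points at ρ of 0 to 0.3. A 20-point loss there would need covariates explaining about half the variance.
- **Main contrast.** Section 2.10 names levels as well as changes, so the loss arises only if change is the contrast that counts.
- **Value of adjustment.** The low correlation that makes change scores costly also makes baseline adjustment worth little: ANCOVA adds 0, 2 and 4 points over a comparison of T2 means at ρ = 0, 0.2 and 0.3.
- **Scope.** SCFA already has a mixed model using both time points. Section 2.11 lists growth and ASQ at 4, 12 and 24 months only, so there is no T1 value to subtract or adjust for.
- **Delivery mode.** Chance imbalance does not invalidate the test. With 40% caesarean births and 10% of variance explained (both assumed), a 20-point imbalance shifts the comparison by 0.20 × √0.10/√(0.4 × 0.6) = 0.13 SD. That is half of the standard error, √(2/30) = 0.26 SD.
- **Test choice and detail.** A rank test is defensible for skewed or zero-heavy abundances, and the power figures assume normality. An analysis plan that is not shown may add adjusted models.

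All of this stands, and it limits the point. It does not remove it: the article itself lists change from T1 as a primary variable, names no main contrast, and calls caesarean birth a risk for dysbiosis while using it only as a subgroup. ANCOVA was at least as powerful as the change score at every correlation examined, so the remedy does not depend on the assumed value.

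**Conclusion.** The concern holds for the microbiome outcomes only, and its size is conditional. If change from T1 is the contrast used and the T1–T2 correlation is about 0.2 to 0.3, the cost against ANCOVA is about 18 to 22 points of power at 30 per arm, falling to 10 points at 0.5 and 2 at 0.7. If T2 levels are compared by Mann–Whitney, the cost is about 2 to 5 points at correlations of 0 to 0.3 and 12 at 0.5. These figures rest on an assumed correlation, a back-calculated effect of 0.723 SD, normality and equal SDs at the two visits.

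The planned test remains valid. What is lost is precision, an effect estimate with an interval, and a contrast fixed in advance.

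One condition limits the remedy. Section 2.7 starts supplementation from birth, while section 3.1 takes the T1 sample as soon as possible after birth or ward admission, within week 1. Nothing shown fixes the sample before the first dose. Adjusting for a post-dose T1 could remove part of the treatment effect, and a change from such a T1 has the same weakness.

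**What to change.** - Name the T2 value of the primary microbiome measure (log ratio of beneficial to pathogenic bacteria, or alpha diversity) as the main contrast, in place of change from T1.
- Analyse it by ANCOVA with the T1 value and delivery mode as covariates, and report the adjusted difference with a 95% CI.
- Use T1 as a covariate only where the sample was taken before the first dose. Otherwise adjust for delivery mode alone. Settle this from recorded sample and dose times before unblinding, and reconcile sections 2.7 and 3.1 on the order of the two.
- Keep Mann–Whitney on T2 as a sensitivity analysis, including for skewed or zero-heavy taxa.
- Leave the SCFA mixed model, growth and ASQ outside this change.

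The cost is analysis text, a check of sampling times, a modelling assumption on the chosen scale and a little more analysis work. No extra infants or samples are needed.
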